### Feasibility and acceptability measures

In order to determine the efficacy of MBCT-C in alleviating internalizing and externalizing problems and enhancing attention in children in single-parent families, a number of important indices will be derived. The first one will be the attrition rate (i.e., the percentage of children who stop receiving treatment) to evaluate the viability of the MBCT-C. The second one will be the engagement and response rates. Moreover, two indices will be tested to determine the acceptability of MBCT-C: first, the children will be evaluated according to their satisfaction with the treatment by MBCT-C-CEQ and then the parent satisfaction will be assessed by MBCT-C-PEQ.

### Interventions

MBCT-C is a manualized group intervention that occurs over 12 weeks. MBCT-C, adapted to children aged 10–12 years, includes mindfulness meditation base with cognitive-behavioral intervention and assists children in managing emotional (e.g., relational and/or familial conflict) and behavioral (e.g., attention problems) difficulties 39 The program aims at fostering awareness of feelings; an intentional focus of attention and emotion regulation through structured activities that are tailored according to the developmental needs of a young child. The same MBCT-C protocol is followed for each session: mindfulness meditation practices, guided sensorial exercises and psychoeducational components. Some of these are: (a) mindfulness of breath practices for enhancing attention and present-moment awareness, (b) body-scan exercises to help focus on physical sensations, (c) sensory-focused activities (e.g., mindful eating, or mindful listening) to help focus on intrapsychic events including thoughts and feelings without judgment; and (d) guided inquiry into intrapsychic events such as thoughts and feelings in an open-minded way [21]. The activities and games will be tailored to the level of the children, and allowing them to learn how to do so through hands-on, playful activities. So children can learn practices of mindful movement or storytelling to connect the concepts of mindfulness with their day-to-day activities.

### Measures

***The Kiddie Schedule for Affective Disorders and Schizophrenia-Present and Lifetime Version (K-SADS-PL)*** is a semi-structured clinical interview to determine 32 psychiatric diagnoses in children and adolescents and includes both parents and children [33]. Diagnostic outcomes derived from this instrument are treated as categorical variables in the analyses. The K-SADS-PL has shown high reliability and validity in the diagnosis of mental health disorders among the youth, and its concurrent validity of current disorders is high. Besides, the test-retest reliability of most diagnoses is good to excellent [35]. The K-SADS-PL Persian version has been proven to be valid and reliable in the Iranian setting. The validation study carried out by Shahrivar, Kousha [36], in Iran revealed that the specificities were over 81% on all disorders, and the sensitivities were between 75 and 100% on the majority of the major diagnoses. Kappa agreement coefficients of most diagnoses were above.4 which illustrates acceptable to strong concordance with test-retest reliability coefficients ranging between.38 and.87.

***The Child Behavior Checklist (CBCL/6–18) and the Youth Self-Report (YSR/11–18)*** are the two tools that assess behavioral and emotional issues in children and adolescents [37]. The CBCL is filled in by the parents or caregivers and the YSR is filled in by the youth. The CBCL has 113 items that are disseminated into eight syndrome scales, which include withdrawal/depression, aggressive behavior, depression/anxiety, somatic complaints, rule-breaking behavior, thought problems, social problems, and attention issues. These scales are divided into two broad categories; internalizing and externalizing behaviors. A study by Abedini, Habibi [26] has revealed that the Persian version of the CBCL/6–18 is quite reliable, with Cronbach alpha coefficients of between.72 and.89. Furthermore, YSR as a youth assessment scale that contains 112 questions aimed at testing youth between the age of 11 and 18; (Fadaei et al., 2009), a validated Persian version of the YSR was employed in the research.

***Mindfulness-Based Cognitive Therapy for Children – Child Evaluation Questionnaire (MBCT-C–CEQ)*** is a 10-item measure assessing satisfaction and engagement with the MBCT-C program ([21]. A 5-point rating scale is used, ranging from 1 (*strongly disagree or very unhelpful*) to 5 (*strongly agree or very helpful*). The overall score is between 10 and 50 where the higher the score the more the satisfaction, categories: 42–50 (*excellent*), 35–41 (*good*), 25–34 (*fair*), 10–24 (*poor*). These scores are treated as continuous variables for analysis. The MBCT-C-CEQ consists of eight open-ended questions, the answers are coded in themes like perceived benefits and suggestions that are summarized by frequencies/frequency of key points in quotes [21].

### Data analyses

The entire analysis will be conducted on the STATA version 18 software. To begin with, descriptive statistics, box plots and scatter plots will be used to analyze the accuracy and distribution patterns of the data sets. 5 percent trimmed mean will be used to compare means to determine outliers. In case of no significant issues, all cases will be stored and regular cleaning will be used.

All analyses will be done using an intention-to-treat approach. Linear mixed-effects models will be used to analyze the changes at baseline, postintervention, and 3-, 6-, 9-, and 12-month follow-ups. All assumptions for the linear mixed-effects models will be assessed before interpreting the results. Normality of residuals will be checked with Q-Q plots and the Shapiro-Wilk test, while homoscedasticity will be evaluated using residuals versus fitted value plots. Multicollinearity among predictors will be examined with variance inflation factors. The independence assumption will be addressed by modeling repeated measurements within participants through random effects structures. If any assumptions are violated, alternative approaches such as generalized linear mixed models, robust standard errors, data transformations, or non-parametric analyses will be considered, based on the nature of the violation.

The models presuppose a crossover design where the waitlist group is provided with MBCT-C at the end of the waiting period. The primary variables will be treatment condition, time, and period, and their interaction. Covariates will include age, gender, baseline scores, and parental stress. The models will adjust for carryover effects, repeated measures, clustering within groups and sequence effects. Model fit will be evaluated via residual diagnostics, which include inspecting residual plots, assessing normality and homoscedasticity, and comparing different covariance structures using Akaike’s Information Criterion and Bayesian Information Criterion. The findings will indicate adjusted mean changes and 95% confidence intervals and effect sizes.

Sensitivity analyses will be done using generalized estimating equations to estimate population effects at various time points. The results of internalizing, externalizing, and attention will be analyzed using a multivariate mixed model and will explain the correlations between them. Several comparison problems will be solved either through Bonferroni correction or hierarchical testing.

Clinical significance will be determined through the reliable change index and responder analysis according to CBCL, PSC and CGI thresholds. The proportion of the participants who will have significantly improved will be compared in both crossover sequences at the end of the intervention and during the follow-up. Maximum likelihood estimation will be used to deal with missing data, assuming that they are missing at random. The findings are in line with the CONSORT requirements of crossover trials.

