### Sample size

The sample size for this study will be determined using G*Power software. According to an a priori power analysis, it is assumed that the smallest clinically meaningful difference corresponds to a small effect size (*Cohen’s d* = .20 [34]), with effect sizes smaller than this considered clinically insignificant. Taking into account the three assessment time points (pre-intervention, post-intervention, and follow-up) and the number of dependent variables, a sample size of 38 participants per condition is necessary (*alpha* = .05, *effect size* = .20, *power* = .95). To account for a 20% dropout rate, the total sample size will be 76 children, who will be randomly assigned to either the MBCT-C group (n = 38) or the WLCG group (n = 38).

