### Current status

As of February 2026, participant recruitment for this crossover randomized clinical trial is actively ongoing and is anticipated to be completed by May 2026, with a target sample size of 76 children from single-parent families. Data collection commenced in December 2025 and is scheduled to continue until June 2026. Due to the crossover design, no participants will receive any study intervention until after recruitment is fully completed in May 2026. Consequently, outcome data related to the primary and secondary endpoints (internalizing, externalizing, and attention problems) remain uncollected at the time of protocol submission, and no study results have been generated or analyzed to date.

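### If the Bonferroni option is used for the three outcomes, Holm's step-down procedure gives the same error control and never less power

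*Protocol article*

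**What the plan says.** On multiplicity, the Data analyses section of the protocol article has one sentence: "Several comparison problems will be solved either through Bonferroni correction or hierarchical testing". It does not say which comparisons form the family, in what order they would be tested, or when each method would apply.

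On the outcomes, the same section says: "The results of internalizing, externalizing, and attention will be analyzed using a multivariate mixed model and will explain the correlations between them". The Current status section groups them as "primary and secondary endpoints (internalizing, externalizing, and attention problems)" without saying which is primary. The Discussion and Conclusions treat the three as separate targets of the intervention.

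On reporting, the Data analyses section says: "The findings will indicate adjusted mean changes and 95% confidence intervals and effect sizes". The intervals are not described as simultaneous or adjusted for multiplicity.

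On size, the Sample size section says that "a sample size of 38 participants per condition is necessary", at alpha .05, effect size .20 and power .95. It does not mention a split alpha.

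**The concern.** Single-step Bonferroni tests each of three outcomes at .05/3 = .0167, whatever the other two show. Holm's procedure sorts the p-values and compares the smallest with .05/3, the next with .05/2 = .025 and the largest with .05, stopping at the first failure. It needs no assumption that Bonferroni does not need. Every rejection by Bonferroni is also a rejection by Holm, and Holm sometimes adds more.

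For testing, then, one of the two named options has a replacement that is never worse. With 38 children per arm, and with an interest in separate statements on three outcomes, the power given up could matter when more than one outcome responds.

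**Working it through.** **The plan's own figure.** The Sample size section gives 38 per arm for d = .20 and power .95. As a plain two-group comparison at two-sided .05, d = .20 needs 650 per arm, and 38 per arm gives power .14. The stated size does not reproduce on that reading. That is a separate matter. The comparison below does not rest on it, because both procedures are run on the same p-values.

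**Inputs from the article.** 38 per arm; alpha .05; three outcomes; d = .20 as the smallest meaningful effect.

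**Assumptions, not in the article.** Two-sided tests; a family made up of the three outcomes at one time point; correlation .6 between baseline and follow-up; correlation r between outcomes of .3 to .7; the same effect on all three unless stated; d = .3 and d = .5 as larger effects; no dropout and no clustering by therapy group unless stated.

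**Formula.** The expected z-value for one baseline-adjusted outcome is d × √(n/2) / √(1 − .6²). With n = 38 this is d × 4.359 / .8:
- d = .5: 2.724
- d = .3: 1.635
- d = .2: 1.090

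The Bonferroni critical value at two-sided .05/3 is 2.394. Power per outcome is therefore about Φ(2.724 − 2.394) = Φ(.330) = .63 at d = .5. The same step gives .22 at d = .3 and .096 at d = .2. Holm's power depends on r and was obtained by simulating three correlated z-tests (400,000 draws per scenario).

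**Results, all three outcomes responding, r = .3 to .7.**

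| d | Per outcome, Bonferroni | Per outcome, Holm | All three, Bonferroni | All three, Holm |
|---|---|---|---|---|
| .5 | .63 | .70–.71 | .33–.44 | .51–.60 |
| .3 | .22 | .26–.27 | .04–.10 | .09–.18 |
| .2 | .096 | .107–.117 | .01–.03 | .02–.06 |

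**With dropout.** At 30 per arm (38 × .8 = 30.4) and d = .5, power per outcome is .51 against .58 to .59, and for all three .21 to .32 against .37 to .47.

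**Taking the stated power at face value.** If each outcome alone had power .95 at .05, power per outcome would be .887 with Bonferroni and .927 to .944 with Holm (r = 0 to .7). For all three it would be .70 to .79 against .85 to .89.

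**Where the gain shrinks or vanishes (d = .5).**
- Two outcomes respond: .63 against .66 for each.
- One outcome responds: .629 against .630 (r = .5).
- At least one rejection: identical in every scenario, because both procedures test the smallest p-value at .05/3.

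**Error rate.** With no effect on any outcome, the family-wise error is the same for both: .0485 at r = 0 and .0444 at r = .5. When one outcome responds (at power .95 alone, r = .3), the chance of a false claim on the other two is .032 with Bonferroni and .046 with Holm. Holm uses more of the allowance but stays within .05.

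**The other named option.** Testing in a fixed order, each step at .05, with d = .5 on all three and r = .5, supports all three with probability .578, against .557 for Holm and .38 for Bonferroni. If instead the first outcome in the order has d = .1 and the other two have d = .5, power for those two falls to .07–.08, against .66 with Holm.

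**The case against.** The strongest reply is that the article states nothing false. Bonferroni is valid, no other section conflicts with it, and no stated power figure rests on a split alpha. This stands, and the point is therefore one of efficiency.

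A reader might infer that the plan pays for multiplicity at .0167 on every outcome. The documents do not support that. The sentence offers hierarchical testing as an alternative, and the family of three at one time point is an inference. The sentence could also concern time-point contrasts, and family and order may be settled in a fuller document that is not shown. Any loss depends on a choice that the article leaves open. In a favourable order, hierarchical testing does as well as Holm or slightly better for all three outcomes. It does not make the point moot, because its power depends on the order and none is given. The Discussion itself concedes that direct evidence on externalizing problems is limited.

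A reader might also infer that the loss under Bonferroni buys nothing at all. That goes too far. Bonferroni has simple matching simultaneous intervals and Holm does not. The weight of this is small here, since the promised intervals are not described as simultaneous.

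Nor does Holm gain most because the outcomes are correlated. At d = .5 the gain for all three falls from 20 points at r = 0 to 16 at r = .7, and the gain per outcome from 9 to 7. What drives the gain is that several outcomes respond to treatment.

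Finally, d = .5 is not a protocol figure. At the protocol's .20 the gain is small.

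**Conclusion.** The point holds conditionally. One of the two named multiplicity options is dominated for testing by a procedure with the same guarantee. If that option is used for the three outcomes and all three respond at d = .5, Holm adds about 7 to 8 points of power per outcome and about 16 to 19 points for supporting all three, over r = .3 to .7. At d = .20 it adds 1 to 2 points per outcome. These sizes rest on the assumed correlations, equal effects and a family of three. The ordering does not: Holm never rejects less than Bonferroni under any of them. The plan as written is valid, so this is a cheap improvement and not a correction of an error.

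**What to change.** In the Data analyses section, replace 'Bonferroni correction' with 'Holm's step-down Bonferroni procedure' wherever a Bonferroni-type correction would be used, including the between-arm tests of internalizing, externalizing and attention problems.

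The cost is a few words and the sorting of three p-values. The family-wise error limit, sample size and conduct are unchanged. If simultaneous intervals are wanted, they will be less simple to construct than under Bonferroni; ordinary 95% intervals are unaffected. The Current status section reports that "outcome data related to the primary and secondary endpoints (internalizing, externalizing, and attention problems) remain uncollected" at submission, so the change could be prespecified without knowledge of results if it is made before those data are seen.

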### Ethical considerations

In line with the Declaration of Helsinki and international research on clinical interventions, the entire procedure will be design as to full fill ethic principles. Written informed consent will be obtained from the children’s parents or legal guardians by the research staff. Furthermore, children will sign their own assent to participate in this study. Details of participation Involvement in this study is voluntary. Individuals will be informed that they are free to leave the study without repercussions. Records will be kept securely in accordance with the General Data Protection Regulation (GDPR). The data collected in this study will be de-identified and privacy will be preserved according to the General Data Protection Regulation. The participants and their parents will also be informed of the procedures for protecting data. Children and their parents will be advised of the aims and methods of the study prior to the commencement of data collection, and parents are free to raise any questions or concerns they might have.

### Current status

As of February 2026, participant recruitment for this crossover randomized clinical trial is actively ongoing and is anticipated to be completed by May 2026, with a target sample size of 76 children from single-parent families. Data collection commenced in December 2025 and is scheduled to continue until June 2026. Due to the crossover design, no participants will receive any study intervention until after recruitment is fully completed in May 2026. Consequently, outcome data related to the primary and secondary endpoints (internalizing, externalizing, and attention problems) remain uncollected at the time of protocol submission, and no study results have been generated or analyzed to date.

## Discussion

The suggested crossover RCT design will involve the effectiveness of MBCT-C in reducing internalizing, externalizing, and attention-related problems in children living in single-parent families. MBCT-C is a child-adapted form of MBCT, which is aimed at enhancing the present-moment awareness, emotional regulation skills, and cognitive control skills of children [21,44].

Prior research indicates that MBCT-C effectively mitigates anxiety, depression, and behavioral problems in adolescents [45,46]. MBCT-C enables children to observe their thoughts and feelings without judgment, and this can disrupt their maladaptive cognitive and emotional processes that contribute to the internalizing and externalizing symptoms [47]. Moreover, MBCT-C is expected to resolve the lack of attentional control, which is typical of children with emotional and behavioral problems [48].

The present study is specifically dedicated to children in single-parent families, the number of which is growing worldwide [49]. The findings may provide information on how mindfulness-based interventions can be adapted to better address the needs of children from single-parent families. Moreover, this study highlights the potentially broad impact of MBCT-C by targeting a range of outcomes, including internalizing symptoms, externalizing behaviors, and attention-related difficulties.

The study may also contribute to the existing literature [26,48,50] by examining potential mechanisms through which MBCT-C influences children’s psychological outcomes. For example, improvements in attentional regulation and emotional awareness may function as mediating processes and offer further insight into how this intervention exerts its effects [51].

This study could increase statistical power by employing within-group comparisons even with a relatively small sample size [52], a problem that is often controversial in parallel clinical trials. However, maintaining long-term participant engagement and eliminating potential carryover effects may be difficult. The current protocol will address these issues by incorporating waiting periods and randomized treatment orders.

Previous research suggests that MBCT-C may be effective in reducing depression and anxiety and improving emotion regulation across different populations [18,26,48]. Although direct evidence for the effects of MBCT-C on externalizing problems remains limited, mindfulness practices may support behavioral regulation and attentional control through their influence on executive functioning [53].

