To close these gaps, the current study will involve a Crossover randomized controlled trial (RCT) with a 12-month follow-up to determine the impact of MBCT-C in children from single-parent families. A 12-month follow-up period was selected to allow for the evaluation of both immediate and longer-term effects of MBCT-C across internalizing, externalizing, and attention outcomes. Previous research on mindfulness-based interventions in children and adolescents suggests that extended follow-up periods are necessary to assess the durability of treatment effects and the emergence of delayed benefits [28]. A shorter follow-up duration may not adequately capture the maintenance or decline of treatment gains, whereas longer follow-up periods may increase the risk of attrition and introduce confounding influences related to developmental changes. Therefore, a 12-month timeframe represents a balanced approach to evaluating sustained intervention effects while maintaining methodological feasibility. The hypothesis is that children who receive MBCT-C will show substantial positive changes in central mindfulness dimensions, including self-acceptance, present-moment awareness, and metacognitive awareness. Moreover, participation in MBCT-C is expected to be associated with reductions in internalizing and externalizing problems. Lastly, the intervention is expected to produce meaningful improvements in attentional functioning. Potential gender differences will also be explored to determine whether treatment effects vary between boys and girls.

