### Participants

The study will include 76 children aged 10–12 years from single-parent families (either the mother or the father), encompassing both genders in Semnan province, Iran. To be eligible for inclusion, participants must demonstrate borderline or clinical levels of attention problems (T-score ≥ 57) and internalizing difficulties (T-score ≥ 60) on a minimum of two out of four subscales from either the Child Behavior Checklist (CBCL) or Youth Self-Report (YSR) [26]. Exclusion criteria include: (a) significant cognitive impairment or developmental disorder, (b) terminal illness with a prognosis of less than six months, (c) chronic psychiatric disorders (e.g., schizophrenia or bipolar spectrum) or neurodevelopmental disorders per DSM-5, assessed via the Kiddie Schedule for Affective Disorders and Schizophrenia-Present and Lifetime Version [K-SADS-PL; 33], (d) change in parental status to an orphan or a two-parent household, and (e) chronic medical conditions impacting psychosocial functioning. A clinical psychologist will conduct psychiatric evaluations using the K-SADS-PL. Written informed consent will be obtained from parents, and children will provide informed assent.

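### For internalizing and attention problems the protocol does not tie its hypotheses to a difference from an untreated waitlist, so regression to the mean after selection on high scores could pass for an effect of MBCT-C

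*Protocol article*

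**What the plan says.** **Selection.** Under Participants, entry requires "borderline or clinical levels of attention problems (T-score ≥ 57) and internalizing difficulties (T-score ≥ 60"), on at least two of four subscales of either the CBCL or the YSR. There is no cut-off for externalizing problems or for mindfulness. The CBCL is also a study assessment (Abstract) and one of the responder instruments (Data analyses, last paragraph).

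**Hypotheses (end of Introduction).** Three are given, none with a comparator: "children who receive MBCT-C will show substantial positive changes in central mindfulness dimensions"; "participation in MBCT-C is expected to be associated with reductions in internalizing and externalizing problems"; and "the intervention is expected to produce meaningful improvements in attentional functioning".

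**Analysis (Data analyses).** The linear mixed model has treatment condition, time, period and their interaction, with baseline score among the covariates. On reporting, the section says: "The findings will indicate adjusted mean changes and 95% confidence intervals and effect sizes". Responder proportions are to be compared between the two sequences at the end of the intervention and during follow-up.

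**Control and visits (Design, Procedure).** Children are randomised to MBCT-C or waitlist. The MBCT-C arm is assessed at T1, after therapy at T2, and in follow-up at T3 to T6. The waitlist arm is listed at T1, then at T3 after its own therapy, then at T4 to T6.

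**Power (Discussion).** "This study could increase statistical power by employing within-group comparisons even with a relatively small sample size". Regression to the mean is not mentioned, including under Limitations.

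**The concern.** A child admitted because a score is high will tend to score lower on retest with no treatment at all. A within-arm test has the null of no change over time, which is a different null from no effect of MBCT-C. For the two domains used for selection, a fall from T1 in treated children would satisfy the hypotheses as worded, even if the programme were inert. Only the comparison with randomised, still untreated children removes this fall, because both arms are selected in the same way.

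The Discussion sentence makes the matter less clear. In a two-way crossover each child contributes a treated and a control period, and within-child comparison does gain precision. Here the MBCT-C arm has no control period: it goes from baseline to therapy to follow-up. With the visits as listed, the waitlist arm has no assessment at the end of its waiting period either. A within-group comparison in this design is therefore a pre-post comparison, and part of its apparent power is power to detect regression to the mean.

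**Working it through.** The protocol gives no figure for regression to the mean, so there is none to reproduce. The check has three parts.

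**1. Can the listed visits separate treatment from time?** Take one intercept, one sequence effect, five visit effects (T2 to T6) and one treatment effect: 8 parameters. Count a child as treated from the end of therapy onward.

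| Visit | MBCT-C arm | Waitlist arm, as listed |
|---|---|---|
| T1 | untreated | untreated |
| T2 | treated | no assessment listed |
| T3 to T6 | treated | treated |

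In every listed row the treatment indicator equals the sum of the five visit indicators. The design matrix has rank 7 of 8, so the treatment effect cannot be separated from time. Adding an untreated waitlist row at T2 brings the rank to 8.

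Counting a child as treated only at the visit straight after therapy would make the term estimable. It would then compare newly treated children with children treated three months earlier, not with untreated ones. The responder comparison at the end of each arm's intervention likewise sets treated against treated.

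**2. How often would pre-post change mislead?**

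Inputs from the protocol: n = 38 per arm, alpha .05 (taken as two-sided), cut-offs 60 (internalizing) and 57 (attention).

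Assumed, because the protocol gives neither: source-population mean m of 50, 55 or 60, and retest correlation r of .7, .8 or .9. Also assumed: SD 10, selection by one cut-off on one score, and the eligibility score used as T1.

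With no treatment effect, a = (cut-off − m)/10 and L = φ(a)/(1 − Φ(a)):

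- expected fall = 10 (1 − r) L
- SD of change = 10 √[(1 − r)²(1 + aL − L²) + 1 − r²]
- noncentrality = fall × √n / SD, referred to a noncentral t with 37 df and critical value 2.026.

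Example (cut-off 60, m = 50, r = .8): a = 1; L = 0.2420/0.1587 = 1.525; fall = 2 × 1.525 = 3.05 points; SD = 10 √(0.04 × 0.199 + 0.36) = 6.07; noncentrality = 3.05 × 6.164/6.07 = 3.10; probability of a significant fall about 86%.

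Lowest cell (cut-off 57, m = 60, r = .9): a = −0.3; L = 0.617; fall = 0.62 points; SD = 4.41; noncentrality = 0.86; probability about 13%.

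Chance that the treated arm alone shows a significant improvement under no effect:

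| Cut-off | Source mean | r = .7 | r = .8 | r = .9 |
|---|---|---|---|---|
| 60 (internalizing) | 50 | 97% | 86% | 55% |
| 60 | 55 | 80% | 61% | 34% |
| 60 | 60 | 50% | 35% | 19% |
| 57 (attention) | 50 | 89% | 72% | 42% |
| 57 | 55 | 63% | 45% | 24% |
| 57 | 60 | 32% | 23% | 13% |

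Simulation agrees to within about one percentage point. The nominal rate in the direction of improvement is 2.5%. On the same simulated data, a two-sample test of change between arms rejects in about 5% of trials (4.5% to 5.6%) in every setting.

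**3. Outcomes not used for selection.** Consider a scale such as externalizing, with an assumed true-score correlation of .6 with the selection scale, source mean 50, cut-off 60 and r = .7 or .8. The within-arm false rate is about 2.5% if measurement errors are independent, and 14% to 43% if they correlate .3 to .5. The effect there is indirect and depends on that assumption.

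**The case against.** The strongest reply is that the plan is a randomised trial with a waitlist control and a model that includes treatment condition and its interaction with time and period. In that model the reported mean changes can be read as changes by condition, or as their contrast. No sentence plans a paired test in the treated arm. The Discussion remark is a loosely worded version of the usual case for crossover designs and is not an analysis rule. Leaving the comparator out of an Introduction is common, and an article may leave the exact contrast to the full protocol or analysis plan.

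Most of this stands. A reader might infer that the protocol will test treated children's change alone, and that regression to the mean would then confirm all its hypotheses. The documents do not support either inference. The reporting sentence is ambiguous, not plainly within-arm. The mindfulness hypothesis and the externalizing part of the second hypothesis concern scales on which nobody is selected.

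The size is also open to challenge. A child may qualify on the YSR and so have a CBCL score that was not selected, which weakens the fall on the CBCL. T1 may be measured separately from screening: Current status says that outcome data remain uncollected although data collection has begun, which could mean this or could mean only that no post-treatment data exist. Either circumstance lowers the percentages.

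What does not stand is that this is only missing detail. The visit schedule is stated twice in the text, under Design and under Procedure, and both times without an untreated waitlist assessment after baseline. Under that schedule the controlled contrast that the model terms suggest cannot be estimated.

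**Conclusion.** The point holds for internalizing and attention problems, two of the three endpoint domains named under Current status. Comparator-free hypotheses, a reported quantity not fixed as a between-arm difference, a claim of power from within-group comparisons, and a listed schedule without an untreated waitlist follow-up leave pre-post change as the only comparison that the text fully supports. Judged that way, an inert programme would appear effective in about 13% to 97% of trials, against about 5% for the randomised difference. The width of the range reflects the assumed source mean and retest correlation, and all of it rests on the eligibility score being the T1 score. If Fig 1 does show a waitlist assessment at T2, the contrast is available and the remaining problem is one of wording. The sample-size calculation is a separate matter, and nothing here depends on it.

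**What to change.** 1. In the Introduction hypotheses and in Data analyses, define the effect as the MBCT-C minus untreated waitlist difference in change from T1 to T2, and report it with its 95% confidence interval.
2. Under Design and Procedure, list a T2 assessment for the waitlist arm, before its therapy begins.
3. Label within-arm changes, including T1 to T3 in the waitlist arm, and all changes after T2 as descriptive and uncontrolled. From T3 on, both arms have been treated.
4. Remove the Discussion sentence that claims power from within-group comparisons.

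The cost is wording in the sections named, plus one questionnaire round for the 38 waitlist children if Fig 1 does not already include it. The precision claim becomes less favourable, because pre-post change no longer counts as evidence of efficacy. Current status says that no child receives the intervention before recruitment ends in May 2026, so according to that timetable the change could be made before any post-treatment data exist.
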